## Abstract

**Background:**

Currently available prophylactic migraine treatment options are limited and are associated with many, often intolerable, side-effects. Various lines of research suggest that abnormalities in energy metabolism are likely to be part of migraine pathophysiology. Previously, a ketogenic diet (KD) has been reported to lead to a drastic reduction in migraine frequency. An alternative method to a strict KD is inducing a mild nutritional ketosis (0.4–2 mmol/l) with exogenous ketogenic substances. The aim of this randomised, placebo-controlled, double-blind, crossover, single-centre trial is to demonstrate safety and superiority of beta-hydroxybutyrate (βHB) in mineral salt form over placebo in migraine prevention.

**Methods/design:**

Forty-five episodic migraineurs (5–14 migraine days/months), with or without aura, aged between 18 and 65 years, will be recruited at headache clinics in Switzerland, Germany and Austria and via Internet announcements. After a 4-week baseline period, patients will be randomly allocated to one of the two trial arms and receive either the βHB mineral salt or placebo for 12 weeks. This will be followed by a 4-week wash-out period, a subsequent second baseline period and, finally, another 12-week intervention with the alternative treatment. Co-medication with triptans (10 days per months) or analgesics (14 days per months) is permitted. The primary outcome is the mean change from baseline in the number of migraine days (meeting International Classification of Headache Disorders version 3 criteria) during the last 4 weeks of intervention compared to placebo. Secondary endpoints include mean changes in headache days of any severity, acute migraine medication use, migraine intensity and migraine and headache-related disability. Exploratory outcomes are (in addition to routine laboratory analysis) genetic profiling and expression analysis, oxidative and nitrosative stress, as well as serum cytokine analysis, and blood βHB and glucose analysis (pharmacokinetics).

**Discussion:**

A crossover design was chosen as it greatly improves statistical power and participation rates, without increasing costs. To our knowledge this is the first RCT using βHB salts worldwide. If proven effective and safe, βHB might not only offer a new prophylactic treatment option for migraine patients, but might additionally pave the way for clinical trials assessing its use in related diseases.

**Trial registration:**

ClinicalTrials.gov, NCT03132233. Registered on 27 April 2017.

**Electronic supplementary material:**

The online version of this article (10.1186/s13063-018-3120-7) contains supplementary material, which is available to authorized users.

## Background

Migraine is a complex, common and debilitating neurological disorder [1] that affects approximately 17% of women and 8% of men in Europe [2]. With a peak incidence during the most productive years of life, migraine not only causes a huge amount of suffering, but also inflicts a substantial amount of costs on society: approximately €18.5 billion per year in Europe alone [3].

Various lines of research suggest that brain energy metabolism abnormalities are likely to be part of migraine pathophysiology [4–9]. Specifically, there is some evidence for reversible abnormalities in mitochondrial functioning in migraine [7, 8, 10]. For example, treatment with riboflavin and coenzyme Q10 has been shown to have migraine-protective effects [4, 7, 9–12], probably via a positive effect on energy metabolism [7, 10]. Lactic and pyruvic acid, markers of mitochondrial disease, have been found to be increased in migraineurs [13]; ^31^P-MRS patterns seen in migraine are consistent with what is seen in mitochondrial disorders [5, 14–16]; and COX-negative fibres typical of mitochondrial diseases have also been seen in some patients with migraine [6]. A breakdown of the resting membrane potential due to lack of ATP could explain cortical abnormalities in excitability, which have been reported in migraine [17–21] and would offer a mechanism by which the trigeminal pain pathway, whose afferents densely innervate the meninges and its associated blood vessels, could be activated or sensitised in migraine. The activation and sensitisation of the trigeminal pain pathway is considered the current understanding for the origin of the migraine headache [22–24].

Despite causing a huge amount of suffering and a substantial amount of costs for society [3, 25], current migraine treatment options are limited and their mechanisms of action are also not completely understood [26]. Most of the prophylactic agents licensed to date are not migraine specific and are additionally associated with significant, sometimes intolerable, side-effects. Furthermore, their migraine-preventive properties tend to be moderate at most. Hence, there is a need for developing alternative anti-migraine therapies.

The ketogenic diet (KD) was developed about 100 years ago after the observation that prolonged fasting has anticonvulsive properties [27]. With its high fat, low carbohydrate and medium protein content, the KD simulates the metabolic effects of starvation. With the advent of antiepileptic medication the rather complicated KD fell out of favour. However, within recent years it has received new interest, in particular since ketone bodies (KBs) might be beneficial for a variety of neurological and even psychiatric disorders due to various different mechanisms [28–30], including improved energy metabolism.

Recently, some case studies [31–34] and a first short proof-of-concept study [35] have demonstrated a reduction in migraine attack frequency, severity and use of acute anti-migraine medication during ketosis—with effect sizes ranging from total absence of attacks [31] to a reduction to 1/5th of the run-in period [35]. In addition, preliminary evidence suggests that the migraine-protective effect may outlast the duration of ketosis [31, 32, 35]. This might be a result of longer-lasting gene expression changes [28, 36]. Elevated KB levels in humans have been shown to be well tolerated for extended periods of time (up to several years) [34, 37–48]. However, a strict KD might not provide a feasible long-term solution for all episodic migraine patients, because patient adherence may be limited and it is not easily implemented in an ambulatory setting.

An alternative means to induce a state of mild to medium nutritional ketosis (0.4–2 mmol/l), irrespective of blood glucose levels, is dietary supplementation with ketogenic substances, such as beta-hydroxybutyrate (βHB) salts [45, 49–52]. This approach could be easily implemented with intake of a ketogenic powder dissolved in water (consisting of a calcium–magnesium–βHB salt three times a day). This intervention seems much more feasible than a strict KD in larger patient populations and avoids the complications of a very restricted high-fat diet. These considerations led us to examine the efficacy and safety of KB mineral salts in migraine prevention within the scopes of a double-blind, randomised, placebo-controlled, efficacy and safety trial with a crossover design.

## Material and methods

### Study design and setting

The study is an investigator-initiated, double-blind, randomised, placebo-controlled, efficacy and safety trial with a crossover design (see Fig. 1) and a treatment period of 36 weeks. It is a single-centre study; all investigations will take place at the clinical trial unit (CTU) of the University Hospital Basel (USB), Switzerland.

**Fig. 1 Fig1:**
[figure not shown]
Flowchart of study design, including timing of measurements and procedures. V = visit

We plan to enrol 45 medium to high-frequency episodic migraineurs (5–14 migraine days/months), with or without aura, aged between 18 and 65 years.

The study period will begin with a 4-week run-in period, during which there is no investigational treatment. The purpose of the run-in period will be observation for baseline comparison. The run-in period will be followed by a 12-week intervention period, when the subjects will receive the investigational medicinal product (IMP) or placebo (orally, three times a day). The intervention period will be followed by a 4-week wash-out and a 4-week second run-in period, during which the subjects will receive no further intervention.

As the study medicament has a half-life of less than 4 h and the outcome measures are based on the last 4 weeks of the 12 weeks intervention only, a 4-week wash-out period was judged to be sufficient. This will be followed by a second 12-week intervention period of the alternative treatment (patients who first received placebo will now receive IMP and vice versa).

Ethics approval has been obtained from the local Ethics Committee (EKNZ 2015-304) and the corresponding competent authority (CA): the National Swiss Drug Agency (2016DR2109). The trial was registered at ClinicalTrials.gov (NCT03132233) prior to starting recruitment. Funding for the study has been received from the Swiss National Science Foundation (SNSF).

### Eligibility criteria

#### Inclusion criteria

##### Visit 1 (prior to the 4-week run in period)

The patient:is between the ages of 18 and 65 years;has been previously diagnosed with migraine (with or without aura) in accordance with the International Classification of Headache Disorders version 3 (ICHD-3) Beta Classification criteria;experiences between 5 and 14 migraine days per month (over the last 4 months) with at least two of the migraines lasting more than 4 h;has an age of onset of migraine younger than 50 years;agrees to refrain from initiating or changing the type, dosage or frequency of any prophylactic medications (exclusive of medications taken for acute relief of migraine symptoms) as well as dietary supplements (such as Q10, riboflavin, etc.) against migraine and for indications other than migraine that in the opinion of the clinician may interfere with the study objectives (e.g. antidepressant, anticonvulsants, beta blockers, etc.) for the duration of the study;has not changed type, dosage or frequency of any prophylactic medications (exclusive of medications taken for acute relief of migraine symptoms) as well as dietary supplements (such as Q10, riboflavin, etc.) against migraine and for indications other than migraine that in the opinion of the clinician may interfere with the study objectives (e.g. antidepressant, anticonvulsants, beta blockers, etc.) for at least 3 months prior to study onset;refrains from making any drastic changes to their diet for the duration of the study, including periods of fasting;agrees to use the study medication as intended, follow all of the requirements of the study including follow-up visit requirements, record required study data in the subject dairy and other self-assessment questionnaires, and is okay with drawing blood samples; andis able to provide written informed consent.

##### Visit 2 (baseline visit, just prior to 12-week intervention)

Before starting the intervention, the study patient must meet all of the following inclusion criteria.

The patient:continues to meet all baseline (Visit 1) eligibility criteria;has experienced between 5 and 14 migraine days; andhas demonstrated compliance with the headache diary during the run-in period.

#### Exclusion criteria

##### Visit 1 (prior to the 4-week run-in period)

Subjects meeting any of the following criteria cannot be included in this research study.

The patient:has a concomitant medical condition that will require oral or injectable steroids during the study;has a history of any significant neurological, psychiatric or other medical condition that in the opinion of the investigator may confound the study assessments (no liver or kidney diseases in particular);has a cardiovascular disease (hypertension in particular) or a history thereof;has a known history of suspected secondary headache;currently takes simple analgesics or non-steroidal anti-inflammatory drugs (NSAIDs) for more than 14 days per 4 weeks or triptans for more than 10 days per 4 weeks for headaches or other body pain;currently takes prescription opioids;has previous diagnosis of medication overuse headache (MoH), which has reverted to episodic migraine within the last 6 months;meets the ICHD-3 Beta Classification criteria for chronic migraine (> 15 headache days per month);has failed an adequate trial (2 months or longer) of at least three classes of a drug therapy for the prophylaxis of migraine;has had surgery for migraine prevention;has received Botox injections within the last 6 months;is pregnant or thinking of becoming pregnant during the study period, or is of childbearing years and unwilling to use an accepted form of birth control;is participating in any other therapeutic clinical investigation or has participated in a clinical trial in the preceding 30 days;belongs to a vulnerable population or has any condition such that his or her ability to provide informed consent, comply with the follow-up requirements or provide self-assessments is compromised (e.g. homeless, developmentally disabled or prisoner); andis thinking to start, change or stop a hormone-based contraception.

##### Visit 2 (baseline visit, just prior to 12-week intervention)

Before starting the intervention, the study patient must meet none of the following exclusion criteria.

The patient:has initiated or changed the type, dose or frequency of any prophylactic medication for indications other than migraine that in the opinion of the clinician may interfere with the study objectives during the 4-week run-in period

### Interventions

#### Experimental intervention

The investigational medicinal product (IMP) used in this clinical trial is d-l-beta-hydroxybutyrate (βHB) in powdered calcium (Ca^2+^)–magnesium (Mg^2+^)–salt form (Ca-Mg-βHB). d-l-Beta-hydroxybutyrate calcium salt (Ca-βHB) dissolves in water (i.e. in the body) into Ca^2+^ and d-l-beta-hydroxybutyrate (βHB), the compound of interest. d-l-Beta-hydroxybutyrate magnesium salt trihydrate (Mg-βHB) dissolves in water (i.e. in the body) into Mg^2+^ and βHB. Also known as beta-hydroxybutyric acid, 3-hydroxybutyric acid or 3-hydroxybutyrate, βHB is an endogenous metabolite with the formula CH_3_CH(OH)CH_2_CO_2_H. It is a beta-hydroxy acid and a keto acid. The IMP was purchased from Ergomax (https://www.ergomaxsupplements.com) in bulk powder of GMP quality and packaged at Hänseler AG (Herisau, Switzerland). It does not contain anything else other than the βHB mineral salts. The flavour is masked using a sucralose-based sugar-free syrup. The daily dose of 9 g Ca-βHB contains 7.54 g of βHB and 1.47 g Ca^2+^, and will be divided into three servings supplied in individual sachets containing 2.51 g βHB and 0.49 g Ca^2+^, respectively. The daily dose of 9 g Mg-βHB contains 6.6 g βHB and 0.77 g Mg^2+^, and will also be divided into three servings supplied in individual sachets containing 2.2 g βHB and 0.26 g Mg^2+^. Both IMPs are provided as a water-soluble powder. During the 12-week intervention period participants will consume the IMPs in three oral doses, to be taken with or after breakfast, lunch and dinner, respectively. This adds up to less than 100 kcal per day. Each serving will raise KB levels for approximately 3 h. To minimise possible gastrointestinal symptoms such as bloating or diarrhoea, patients are instructed to increase the dosage over time, starting with half the dose during the first week before reaching the maximum dosage by day 7.

Elevated ketone body (KB) levels have been shown to be well tolerated for extended periods of time (up to several years) [31–35, 37–49]. During fasting, the healthy adult is capable of producing up to 185 g of KBs [53]. Previously, orally administered sodium βHB salts with higher doses ranging between 0.5 and 1 g per kg have been shown to be tolerated in both the short term [39, 50, 54, 55] and the long term [45, 49, 52, 56, 57] with no significant side-effects. The rather conservative dose of 18 g βHB mineral salt per day (as compared to endogenous production during starvation) was determined largely by the mineral load of Mg^2+^ and Ca^2+^, which we wanted to keep within acceptable ranges. Not going over the suggested maximum supplemental guidelines meant 9 g of Mg-βHB and 9 g of Ca-βHB, respectively. A similar dose of 5 g βHB/day was shown to lead to a modest elevation in blood KB (up to 0.4 mmol/l) [52], supporting the safety of our chosen dose. A Ca-βHB and Mg-βHB salt was chosen to avoid the potentially negative long-term consequences of high sodium intake.

To the best of our knowledge, no human controlled trials using βHB mineral salts have been done, either for migraine or for any other indication, and there seems to not yet be other human published data on specifically Ca-βHB and Mg-βHB. However, recently, βHB supplements, mostly in mineral salt form similar to our IMP, are being produced and sold in the USA, marketed as a sport/life-style supplement. A couple of million servings with a similar dosing to our IMP have been consumed without any incidents reported.

#### Control intervention

The placebo powder consists of mannitol, a sugar alcohol, which has the same texture, colour and packaging. Taste and smell are masked in the applied form (both are diluted in sugar-free syrup) and therefore similar. It is used by the USB Pharmacy as the standard placebo substance. In higher doses it can also lead to gastrointestinal symptoms [58], which means it has similar potential side-effects to the IMP.

#### Packaging, labelling and supply

The IMP and placebo are provided in sachets containing either one dose of Ca-βHB (3 g) or one dose of Mg-βHB (3 g), respectively, in powder form (see earlier). The whole supply for the study (ca. 3 kg per patient, > approximately 70 kg IMP and 70 kg placebo in total) will be delivered to and stored at the pharmacy of the University Hospital Basel. Patients will be provided with sufficient quantity to last from each visit to the next. The IMP will be labelled in accordance with regulatory requirements.

#### Storage conditions

The IMP is stored at room temperature. After delivery it will be stored at the USB Pharmacy until the end of the study.

#### Concomitant interventions (treatments)

The use of analgesics and triptans is allowed for less than either 14 days (analgesics) or 10 days (triptans), respectively, per month. They are not predicated to have an effect on the study outcomes. Steroids (oral or injectable) as well as prescription opioids are not permitted for the duration of the study period, including run-in and follow-up. Migraine-related surgery and Botox injections within the last 6 months are also not permitted. Prophylactic medications (exclusive of medications taken for acute relief of migraine symptoms) as well as dietary supplements (such as CoenzymeQ10, riboflavin, etc.) against migraine and for indications other than migraine that in the opinion of the clinician may interfere with the study objectives (e.g. antidepressant, anticonvulsants, beta blockers, etc.) are permitted as long as the type, dosage or frequency is not changed for the duration of the study and has not been changed at least 3 months prior to study onset. Hormone-based contraception is permitted as long as the patient does not intend to start, stop or change it for the duration of the study and at least 3 months prior to the intervention. Other hormonal treatment is not permitted.

### Outcome measures

#### Primary outcome measure

##### Mean change from baseline in number of migraine days (meeting ICHD-3 criteria) during the last 4 weeks of intervention compared to placebo

In order to assess the therapeutic efficacy of externally induced mild ketosis over placebo in migraine prevention, a detailed headache diary in pen and paper form is used to record the change in monthly migraine frequency. The headache diary includes: month, days 1–31, distinction migraine/headache, pain intensity (Likert scale 0–10), medication, dosage, treatment effectiveness of acute medication used (Likert scale 0–10), migraine-associated symptoms, days with menstruation and potential trigger factors (if known).

A day with head pain will only be classified as a migraine day if it meets ICHD-3 classification criteria. According to the International Headache Association and the European Medical Association Guidelines, the recommended measure to assess migraine frequency reduction is the change in migraine days per 4 weeks compared to baseline. This approach has one major advantage over the other frequently used method of recording the number migraine attacks: attack duration is also taken into consideration.

#### Secondary outcome measures

##### Mean change from baseline in number of headache days of any severity (meeting ICHD-3 criteria) during the last 4 weeks of intervention compared to placebo

The same headache diary in pen and paper form is used to record the change in 4-week headache frequency. A day with headache will only be classified as a headache day if it does not meet ICHD-3 migraine classification criteria. According to the International Headache Association and the European Medical Association Guidelines, the change in migraine days versus headache days per 4 weeks compared to baseline should be recorded separately in migraine patients who experience both headache types.

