#### Fixed sample size estimation

##### Assumptions

Sample size estimation is based on the following assumptions:We expect the baseline number of migraine days per 4 weeks to be 10 days in our patient population.Placebo effect: based on recent findings [64], we assume a rather strong placebo effect of 32% reduction in the primary endpoint. This corresponds to an absolute reduction of 3 migraine days per 4 weeks.IMP effect: synthesising previous findings [4, 64] and our pilot data [65], we aim to detect a difference of 2 days between placebo and IMP.We assumed the absolute reduction in migraine days to be normally distributed with a standard deviation of 3 days.We assume a conservative intra-patient correlation between IMP and placebo of 0.4.Drop out: a high drop-out rate of 30% is assumed.

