##### Secondary analysis

The secondary (exploratory) objectives are to assess the therapeutic efficacy of externally induced mild ketosis by the IMP regarding the following secondary endpoints:change in number of headache days of any severity from baseline (meeting ICHD-3 criteria) during the last 4 weeks of intervention;change in number of headache days of any severity from baseline (meeting ICHD-3 criteria) during the last 4 weeks of follow-up;change in consumption of acute migraine medication from baseline (analgesics or triptans)— measured in days with acute headache medication use—during the last 4 weeks of intervention;change in average migraine intensity from baseline—assessed with a VAS from 0 to 10 for each migraine episode—during the last of 4 weeks of the intervention period; andchange in disability from baseline—assessed with the Migraine Disability Assessment (MIDAS) and the Headache Impact Test (HIT-6)—to the last of 4 weeks of the intervention period.

All of these secondary endpoints will be analysed as described for the primary endpoint with the corresponding baseline measure as covariate, if available.

All secondary analyses are done on the ITT set.

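### The any-severity headache-day endpoint counts only non-migraine days, so it has no clear direction of benefit, and no listed endpoint estimates total headache days

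*Protocol article*

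**What the plan says.** The heading under Secondary outcome measures reads "Mean change from baseline in number of headache days of any severity (meeting ICHD-3 criteria) during the last 4 weeks of intervention compared to placebo". Below that heading, the text narrows the count: "A day with headache will only be classified as a headache day if it does not meet ICHD-3 migraine classification criteria". The reason given is guideline advice that changes in migraine days and headache days "should be recorded separately in migraine patients who experience both headache types".

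The primary outcome section supplies the other half of the split: "A day with head pain will only be classified as a migraine day if it meets ICHD-3 classification criteria". A day with head pain therefore falls in one count or the other, never in both.

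The restriction does not appear elsewhere. The abstract says "Secondary endpoints include mean changes in headache days of any severity". The Secondary analysis section lists "change in number of headache days of any severity from baseline (meeting ICHD-3 criteria) during the last 4 weeks of intervention", plus a second version with the same name for the last 4 weeks of follow-up. It then states: "All of these secondary endpoints will be analysed as described for the primary endpoint with the corresponding baseline measure as covariate, if available". No listed endpoint is defined as the sum of migraine and non-migraine headache days.

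**The concern.** Two problems follow.

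First, the variable is not uniquely fixed. An analyst working from the abstract or the Secondary analysis section could count every headache day. One working from the outcome definition would count only days that fail migraine criteria. These are different variables and can give different answers. If the ambiguity survives to the analysis, the choice could be made after results are known.

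Second, under the written definition the endpoint is analysed as an efficacy outcome, yet a lower value is not plainly better nor a higher value plainly worse. A migraine day that becomes a milder headache leaves the primary count and enters this one. A migraine day that becomes pain-free does not register here at all. A reader of the results table who expects a fall to mean benefit could be misled.

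This matters more in migraine because, as the Discussion acknowledges, patients themselves must tell migraine from other headache. Total headache days does not change when a day is merely relabelled, so it is the natural companion to the primary result.

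**Working it through.** **Inputs from the protocol (Sample size estimation)**
- Baseline: "We expect the baseline number of migraine days per 4 weeks to be 10 days in our patient population".
- Placebo reduction: 3 migraine days per 4 weeks.
- Target difference between IMP and placebo: 2 days, so an IMP reduction of 3 + 2 = 5 days.
- SD of the reduction 3 days, within-patient correlation 0.4, two-sided paired t test at 0.05, power 90%, drop-out 30%.

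**The plan's own figure first.** SD of the within-patient difference = √(2 × 3² × (1 − 0.4)) = √10.8 = 3.286. For a 2-day difference, the exact noncentral-t power is 0.896 at n = 30 and 0.906 at n = 31. Allowing for drop-out, 31 / 0.70 = 44.3, rounded up to 45. The stated 31 evaluable and 45 recruited reproduce. They rest on migraine days only, so nothing below changes them.

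**Assumptions not given in the protocol**
- q is the share of the 2 extra avoided migraine days that become non-migraine headache days. It is unknown, so the full range from 0 to 1 is shown.
- Other non-migraine headache days do not change (relaxed below).

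**Formulas (IMP minus placebo, days per 4 weeks)**
- Migraine days: −2
- Non-migraine headache days, the endpoint as defined: +2q
- Total headache days: −2 + 2q = −2(1 − q)

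| q | Migraine days (primary) | Non-migraine days (as defined) | Total headache days |
|---|---|---|---|
| 0 | −2.0 | 0 | −2.0 |
| 0.25 | −2.0 | +0.5 | −1.5 |
| 0.5 | −2.0 | +1.0 | −1.0 |
| 1 | −2.0 | +2.0 | 0 |

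**By arm.** Applying one share to all avoided migraine days under both treatments gives the same differences. At q = 1, placebo gains 3 non-migraine days and IMP gains 5, a difference of +2. Total headache days change by −3 + 3 = 0 on placebo and −5 + 5 = 0 on IMP, a difference of 0.

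**Relaxing the second assumption.** If other non-migraine headaches fall by h days more on IMP than on placebo, the endpoint as defined becomes 2q − h and the total becomes −2(1 − q) − h. The endpoint as defined goes against IMP only when 2q exceeds h. The protocol gives neither quantity.

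**Recovering the total.** The two counts are mutually exclusive and together cover all headache days, so the total for each patient and period is their sum. At q = 1 this gives −2 + 2 = 0, which exposes pure reclassification. What the two planned models do not provide is an estimate and confidence interval for that sum: each adjusts for its own baseline value, and neither yields the covariance between the two estimates. The summed count has to be modelled in its own right.

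**The case against.** The strongest reply is that the separate count is deliberate. The protocol defines it, cites guideline advice for it, and can be read so that any severity refers to pain grade, not headache type; the diary records these as separate fields. On that reading the heading and its definition are compatible. This stands in part: separate recording is not an error, and the heading has more than one reasonable reading. It does not settle the matter, because the abstract and the Secondary analysis section carry the label with no restriction, and separate recording does not prevent analysing the total as well.

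A reader might infer that the trial cannot detect a mere relabelling of migraine as headache. The protocol does not support that. The total is recoverable from the diary, and the two results side by side would show conversion. Days with acute medication, MIDAS and HIT-6 also do not depend on how a day is labelled, and the Discussion describes a patient briefing, a neurologist's consultation and a carefully constructed diary to limit misclassification. These are mitigations or indirect measures, however; none estimates total headache days.

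A reader might also infer that an effective product must score worse on this endpoint. That does not follow either. With no conversion the difference is 0, and a fall in other headaches could make it neutral or favourable.

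Finally, the protocol calls these secondary objectives exploratory, which limits the consequences.

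**Conclusion.** The point holds as one of definition and interpretability. The name and the definition can be read as different variables, the restriction appears in only one of the three places, and the non-migraine count is analysed as efficacy although it has no clear direction of benefit by itself. For the planned 2-day migraine benefit, the endpoint as defined would differ by 0 to +2 days (IMP minus placebo), while total headache days would differ by −2 to 0. Both ranges rest on an assumed conversion share between 0 and 1 and on other non-migraine headaches staying constant. They illustrate direction and are not a forecast. The primary endpoint, its hypothesis and the sample size are unaffected.

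**What to change.** Before unblinding:

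1. Define the any-severity endpoint as all days with headache in the 4-week window, migraine plus non-migraine, summed for each patient and period and analysed with the model already planned, using the matching all-headache baseline as covariate.
2. Keep the non-migraine count as a separately labelled descriptive endpoint, to be read beside migraine days. This preserves the separate recording that the protocol wants.
3. Use the same wording in the abstract, the Secondary outcome measures section and the Secondary analysis section, including the follow-up version listed there.

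The cost is a wording change and one additional analysis. The diary already distinguishes migraine from other headache by day, so no new data are needed.
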